### Blinding, randomisation and treatment allocation

Participants who purchased the PHC and who consented to participate in part B will be electronically randomised to receive the additional lifestyle counselling. Randomisation will be stratified by local clinic, and block randomisation will be used with block sizes of 4 within each stratum. The health coach will subsequently implement the appropriate intervention.

Although blinding is not possible for the participants and the health counsellors delivering the intervention, the data analyses will be performed in a blinded format through preparation of the dataset by an independent researcher.

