## Methods/design

### Study design

This study consists of two integrated trials. The first trial is a non-randomised two-armed controlled pre-test/post-test superiority trial (part A). Of one of those arms, participants can enter the second trial, which is a randomised controlled pre-test/post-test superiority trial (part B), on the condition that they consent to participate. In order to obtain sufficient participants for part B, participants in part A will be distributed in a 1.5:1 ratio. Participants will be randomised at a 1:1 ratio in part B. This results in three study arms (Fig. 1). However, due to eligible participants of part A potentially not consenting to participation in part B, study arm 2 can again be considered as two study arms: participants in arm 2a have consented to participate in part B whereas participants in 2b have not (see Fig. 1 for a visualisation).

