### Participants and recruitment

Participants for part A of the study will be recruited from the regular customers at local prevention clinics who have purchased one of the following products:Product 1: *personalised health check* (PHC). The PHC consists of the Health Potential® service (future health) and a general health check of the customer’s current health.Product 2: a general health check of current health only (GHC).

Potential participants will be informed of the study by the local responsible investigator of each clinic. Eligible participants for part A are apparently healthy individuals aged 18 and over, with a Dutch language level similar to language proficiency level B2, not currently following any prescribed dietary or other guidelines, not pregnant or trying to become pregnant, authorised to make autonomous decisions, able to independently visit the counselling clinic, and have Internet access and an email address. Participants who purchased product 1 are eligible to take part in part B of the study. Enrolment will be open for 1 year.

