### Sample size and power calculation

The sample size calculation is based on the proportion of participants who have changed their behaviour (being in the action/maintenance stage of behaviour change; see ‘Study parameters’) for at least three of the received advices at follow-up in the overall analysis. The type I error rate was set at 0.05 and an additional 20% was added to compensate for loss to follow-up in part A.

*Part A*: The smallest difference is expected between arms 2 and 3. It is estimated that with (291 + 20%=) 350 participants in each arm, part A has a power of 80% to detect a proportion of 0.3 in arm 2 versus a proportion of 0.2 in arm 3.

*Part B*: Study arm 1 will be compared to arm 2a. It is then estimated that with (160 + 20%=) 192 participants in each arm, part B has a power of 80% to detect a proportion of 0.45 in arm 1 versus a proportion of 0.3 in arm 2a. As in part A 548 participants will be included in the PHC condition, this will give a margin of (548 − 384=) 164 for participants not consenting to participate in part B. Together this results in a total number of participants of (192 + 350 + 350=) 892.

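### Part B's single published block size of 4 within each clinic lets anyone who knows the earlier allocations deduce up to a third of them, an avoidable risk of selection at consent

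*Protocol article*

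**What the plan says.** The section on blinding, randomisation and treatment allocation in the protocol article fixes the scheme for part B. "Randomisation will be stratified by local clinic", and "block randomisation will be used with block sizes of 4 within each stratum". The study design section adds the ratio: "Participants will be randomised at a 1:1 ratio in part B". Each clinic therefore has its own sequence of blocks, each holding two allocations to either arm.

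The order of events is also given. Buyers of the personalised health check "who consented to participate in part B will be electronically randomised to receive the additional lifestyle counselling", so consent comes first. Then, "The health coach will subsequently implement the appropriate intervention". The same section concedes that "blinding is not possible for the participants and the health counsellors delivering the intervention"; only the data analysis is blinded.

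On recruitment, the article says "Potential participants will be informed of the study by the local responsible investigator of each clinic". That sentence stands in text about entry to part A. The article does not say who seeks consent to part B, or whether that person can see earlier allocations. The planned size of part B is given as "with (160 + 20%=) 192 participants in each arm", which makes 384 in all.

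**The concern.** Electronic randomisation after consent hides the list and the next assignment. It does not stop deduction from allocations already carried out. In an open trial those allocations are visible to the people who deliver them. With a constant block of 4, once one arm has used its two places, the rest of the block is known.

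This matters for three reasons.

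- Part B is the only randomised comparison in the study, and its advantage over part A rests on allocation that cannot be foreseen.
- Consent to part B is a separate voluntary step. The sample size section allows for 164 of 548 personalised-health-check participants not consenting, so there is room for influence on who consents and when.
- The design rationale expects clients to differ in prior motivation. Motivation plausibly bears on the outcome behind the sample size, which is being in the action or maintenance stage for at least three pieces of advice. A recruiter who foresaw the next allocation could, even without intent, encourage or delay consent accordingly.

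**Working it through.** **Inputs.** From the randomisation section: block size 4, constant, within clinic. From the study design section: ratio 1:1. From the sample size section: 160 per arm before loss and 192 after, proportions 0.45 and 0.30, power 80%, type I error 0.05 (taken as two-sided, since the article does not say).

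**The plan's own figure.** The article gives no predictability figure. Its part B sample size can be reproduced with the unpooled normal approximation:

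n = (1.960 + 0.842)² × (0.45 × 0.55 + 0.30 × 0.70) / (0.45 − 0.30)² = 7.849 × 0.4575 / 0.0225 = 159.6, so 160.

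160 × 1.2 = 192 per arm, and 2 × 192 = 384.

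**Allocations known with certainty.** A 1:1 block of 4 has 6 equally likely orders. In two of them (AABB, BBAA) the third and fourth allocations are determined. In the other four only the fourth is.

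(2 × 2 + 4 × 1) / 6 = 8/6 = 1.333 per block; 1.333 / 4 = 33.3%.

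384 / 4 = 96 blocks; 96 × 1.333 = 128 allocations. Incomplete final blocks lower this slightly. The number of clinics is not given, so the reduction cannot be computed.

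**Best-guess success.** Guess the arm with more places left, and toss a coin when they are equal.

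| Position in block | Probability of a correct guess |
|---|---|
| 1 | 1/2 |
| 2 | 2/3 |
| 3 | 1/3 × 1 + 2/3 × 1/2 = 2/3 |
| 4 | 1 |

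The sum is 2.833, and 2.833 / 4 = 70.8%, against 50% by chance.

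**Alternatives.** The fixed sizes were enumerated. The mixed sizes were simulated with 2,000 sequences of length 40 and 2,000 of length 96. In the simulation the guesser sees all earlier allocations and knows the set of sizes, but not which size is in use.

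| Scheme | Known with certainty | Best guess correct |
|---|---|---|
| Fixed 4 | 33.3% | 70.8% |
| Fixed 6 | 25.0% | 68.3% |
| Fixed 8 | 20.0% | 66.6% |
| Random 4, 6 | about 5.5% | about 69% |
| Random 4, 6, 8 | about 2.2% | about 68% |

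**What selection could do (illustration only; the shifts are assumed and not in the documents).** Suppose one third of each arm's allocations are foreseeable, and selection moves the success probability in those places by d, upwards in one arm and downwards in the other. The bias in the difference is 2 × d / 3. With a true rate of 0.30 in both arms and 160 per arm, the standard error is √(2 × 0.30 × 0.70 / 160) = 0.0512.

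| Assumed d | Bias | Two-sided type I error |
|---|---|---|
| 0.02 | 0.013 | about 6% |
| 0.05 | 0.033 | about 10% |
| 0.10 | 0.067 | about 26% |

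**The case against.** The strongest reply is that one third is a ceiling. It needs one person who takes part in part B consent, knows the block size, and knows every earlier allocation in the current block at that clinic. The article names a local investigator who informs people, a health coach who implements the allocation, and certified counsellors who deliver the sessions. It does not say that these are the same people or that they share information. A reader might infer that clinic staff will foresee a third of allocations, or that enrolment is biased. The documents support neither reading. This objection stands, and it is why the point is put conditionally.

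Other parts of the reply also stand:

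- The sentence about the local investigator belongs to part A recruitment and does not show who seeks consent to part B.
- Purchase of the product alone gives eligibility for part B, so no discretionary entry criterion is described. What remains is the timing or encouragement of consent.
- Consent before electronic randomisation is already stated. Baseline questionnaires are set at six weeks before counselling starts, and nothing suggests that allocation precedes them.
- Additional counselling is a secondary aim; the primary aim is addressed in the non-randomised part A.
- Reporting bias from unblinded self-report is a separate matter that block size does not change.
- Measured baseline imbalance can be checked, though unmeasured motivation cannot.

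One argument does not dispose of the point. The article is condensed, and details of concealment may sit in the deposited full protocols, so their absence is no finding. The single block size of 4, however, is a choice stated and published here.

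**Conclusion.** The point holds as an avoidable design weakness. A constant, published block of 4 within clinic, in an openly delivered 1:1 trial, makes up to 33.3% of allocations deducible in expectation (about 128 of 384). This assumes full knowledge of the earlier allocations in each block and complete blocks. The article does not establish the first condition, so no actual rate of prediction and no actual bias can be claimed. The type I error figures above show only what assumed shifts would do.

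The matter is worth acting on because the remedy is nearly free and the article's trial status section says the trial is still in preparation. It should not be oversold: the gain lies in removing near-certain foreknowledge, while the advantage of an informed guess shrinks only from 70.8% to about 68%.

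**What to change.** Replace the single block size with randomly varying sizes within clinic, for example 4, 6 and 8. Do not disclose the sizes to the clinics, and remove them from any document the clinics use before enrolment. Keep the stated order of consent first and electronic randomisation after.

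A larger fixed block is not an adequate substitute, because a fixed block of 8 still leaves 20.0% of allocations certain.

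The cost is a setting in the randomisation system and a short change to the protocol text. The sample size does not change. The largest difference between arms that an unfinished block can leave in a clinic is half the block size, so it rises from 2 to 4. This matters only in small clinics.

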### Investigational behavioural intervention

Part A does not contain an intervention. In part B, the participant receives additional lifestyle counselling. The lifestyle counselling consists of four additional personal face-to-face sessions with a purpose-trained lifestyle counsellor. The counselling follows four phases matching four core questions [22] and is delivered using principles of motivational interviewing [23, 24]:Counselling phase 1: “Am I at an increased risk because of my lifestyle?”Counselling phase 2: “Which choices are suitable for me?”Counselling phase 3: “How do I translate my choices to behaviour?”Counselling phase 4: “How can I maintain my change in behaviour?”

All lifestyle counselling sessions are done by the same certified lifestyle counsellors for one participant. The sessions take place at *t* = 0 week, *t* = 1 week, *t* = 4 weeks and *t* = 12 weeks (see Fig. 1, sessions 2–5) and will last approximately 45–60 min per session.

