### Statistical analysis

Where appropriate, the analyses will be performed according to an intention-to-treat (ITT) approach (part B only) and per-protocol approach. Data will be analysed using STATA (StataCorp. Stata Statistical Software, College Station, TX: StataCorp LP). Statistical significance is assumed at a *p* value of 0.05, and no correction for multiple testing will be applied.

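### Part B's stated 80% power assumes independent participants and makes no allowance for counsellor clustering in arm 1

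*Protocol article*

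**What the plan says.** All references are to the protocol article.

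- **Sample size and power calculation.** "The type I error rate was set at 0.05". For the randomised comparison, "part B has a power of 80% to detect a proportion of 0.45 in arm 1 versus a proportion of 0.3 in arm 2a". The number is built up as "160 + 20%=) 192 participants in each arm". No design effect, ICC or number of counsellors appears.
- **Investigational behavioural intervention.** Arm 1 has four additional individual sessions of 45 to 60 minutes, using motivational interviewing. On who delivers them: "All lifestyle counselling sessions are done by the same certified lifestyle counsellors for one participant".
- **Study setting.** The extra counselling comes from certified counsellors in South-Limburg. Their number is not given.
- **Blinding, randomisation and treatment allocation.** "Randomisation will be stratified by local clinic", in blocks of 4.
- **Statistical analysis.** Intention-to-treat (Part B only) and per-protocol approaches, Stata and a 0.05 significance level are named. No test or model for Part B is given.
- **Background.** The Health Potential result is itself delivered face to face by a counsellor, so arm 2a also has some counsellor contact.

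**The concern.** The component tested in Part B is delivered by individual counsellors, and only to arm 1. That is a partially nested design: arm 1 participants are grouped by counsellor, while arm 2a participants have no such grouping for the extra sessions. If some counsellors achieve more behaviour change than others, participants of the same counsellor resemble one another, and the variance of the arm 1 proportion exceeds the binomial variance used for sizing.

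Two things are at stake. First, the trial may have less than the stated 80% chance of detecting 0.45 against 0.30. Second, if the eventual analysis ignored counsellor and counsellor effects did vary, confidence intervals would be too narrow. The second point depends on an analysis that the article does not describe; the first concerns a figure that it states.

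**Working it through.** **Inputs from the article:** proportions 0.45 (arm 1) and 0.30 (arm 2a), alpha 0.05, power 80%, 160 evaluable per arm, 1:1 allocation. The article does not say whether the test is two-sided. Two-sided is assumed, because a one-sided calculation gives 128 per arm and does not fit.

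**Inputs assumed:** 5 to 20 counsellors (k) with equal caseloads; ICC 0.01 to 0.05 in arm 1; no clustering in arm 2a.

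**Step 1: reproduce the stated number.** With unpooled variance and independent participants,

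n = (1.960 + 0.842)² × (0.45×0.55 + 0.30×0.70) / 0.15² = 7.849 × 0.4575 / 0.0225 = 159.6, so 160.

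This matches the plan exactly and leaves no room for a design effect. The pooled-variance version gives 163 per arm, or 79.4% power at 160. The article's 192 is 160 × 1.2.

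**Step 2: is sharing of counsellors real?** Arm 1 has 192 participants and 192 × 4 = 768 extra sessions. Caseloads of one would need about 192 purpose-trained counsellors in one region. The size of the caseload is unknown, but its existence is hardly in doubt.

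**Step 3: inflate the arm 1 variance only.** Average caseload among those analysed is m = 160/k, and the design effect is DE = 1 + (m − 1) × ICC. With Φ the standard normal distribution function,

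power = Φ(0.15/SE − 1.960), SE = √[(0.2475 × DE + 0.21)/160].

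For 10 counsellors and ICC 0.02: m = 16, DE = 1 + 15 × 0.02 = 1.30, SE = √(0.53175/160) = 0.0577, 0.15/SE = 2.60, power = Φ(0.64) = 74.0%.

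| Counsellors | Caseload m | ICC | DE | Power, unpooled | Power, pooled |
|---|---|---|---|---|---|
| any | – | 0 | 1.00 | 80.1% | 79.4% |
| 20 | 8 | 0.01 | 1.07 | 78.6% | 78.0% |
| 10 | 16 | 0.02 | 1.30 | 74.0% | 73.5% |
| 8 | 20 | 0.05 | 1.95 | 62.5% | 62.6% |
| 5 | 32 | 0.05 | 2.55 | 54.3% | 54.8% |

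The two variance conventions differ by less than one point, so the choice of formula does not drive the result.

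**Step 4: what an analysis that ignored counsellor would do.** If counsellor effects vary but average to no effect, the actual two-sided error of a nominal 0.05 test is 2 × [1 − Φ(1.960 × √(2/(1 + DE)))]. That is 0.068 at DE 1.30 (m = 16, ICC 0.02) and 0.107 at DE 1.95 (m = 20, ICC 0.05).

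**Step 5: clinic strata, checked separately.** A simulation used 160 per arm, 4 to 16 clinics and an assumed clinic standard deviation of 0.6 on the log-odds scale. An unstratified test had a type I error of 0.041 to 0.044 and power of 74 to 75%. A Cochran-Mantel-Haenszel test had 0.046 to 0.051 and about 77%. Leaving clinic out is therefore conservative and loses a little power.

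**The case against.** The strongest objections, and what remains of each:

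- **The article commits to no analysis.** A two-proportion formula used for sizing does not bind the trial to an unadjusted test, and clinic or counsellor terms may sit in the full protocols, which the article says are deposited elsewhere. This stands. A reader might infer that Part B will be analysed by a plain two-proportion test and that its intervals are already wrong; the article supports neither. It also does not say that counsellor identity goes unrecorded.
- **Clinic strata.** A reader might count neglect of the clinic strata as a further reason why power is overstated or error inflated. The simulation shows a conservative test, the opposite direction from counsellor clustering, and the article does not say that clinic will be left out.
- **The sentence on counsellors describes continuity within a participant, not caseload.** True. Shared caseloads are inferred from 192 participants and a regional pool of counsellors. The inference is strong, but caseload and ICC remain assumptions, and at the favourable end the loss is only one to two points.
- **Arm 2a also meets a counsellor.** If the same people serve both arms, some of the shared variation may cancel in the difference. This may reduce the loss, but it does not remove variation in how well the four extra sessions are delivered.
- **Type I error is not inflated if counselling does nothing for anyone through any counsellor.** Correct. Inflation needs counsellor effects that differ, and inference beyond the particular counsellors in the trial.

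**Conclusion.** The point holds as a statement about the power calculation. The 160 per arm is the independent-participants figure, and the design described elsewhere in the article makes independence in arm 1 doubtful. Under the assumed 5 to 20 counsellors and ICC 0.01 to 0.05, power at 160 evaluable per arm lies between about 78% and about 55%, with about 74% in the middle case. Where the trial falls in that range depends chiefly on the number of counsellors, which the sponsor should know, and on an ICC that has to be assumed. The figures also assume equal caseloads and no counsellor clustering in arm 2a. Too-narrow intervals are a conditional risk: they arise only if the analysis ignores counsellor and counsellor effects vary.

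**What to change.** 1. Restate the Part B power with the planned number of counsellors, over ICC values of 0.01 to 0.05, inflating the arm 1 variance. Say whether counsellors also serve arm 2a.
2. Ensure that counsellor identity is recorded for every participant. The article reports the trial as still in preparation, so this can be in place from the first enrolment; it may be hard to reconstruct later.
3. Confirm in the full protocol or analysis plan that the Part B analysis allows for counsellor, for example by cluster-robust variance or a random effect. The form should match the design: a counsellor effect in arm 1 only if arm 2a is not served by the same counsellors, and a structure covering both arms if it is. With few counsellors, use a small-sample correction. Include clinic as a stratification factor.

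The cost is one recorded variable, a short power table, some wording in the analysis plan, and a less favourable stated power. No clinical procedure changes.

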### Study parameters

To study the effect of Health Potential® on behaviour change, a conceptual framework has been developed (Fig. 2), based on a previously proposed framework for PGT by Bloss et al. [8] and the I-change model [25]. The framework consists of two steps that are relevant for eventual behaviour change: (1) purchasing Health Potential® and (2) behaviour change as a result of Health Potential®. Determinants included in both steps are based on the literature on PGT [20, 26–36] and the I-change model [37].

**Fig. 2 Fig2:**
[figure not shown]
Flow chart of the study

All parameters (Table 1) are measured using online questionnaires, as part of part A of the study, and are saved in a coded format. Measurements take place at *t* = −6 weeks (baseline), *t* = 0 week, *t* = 1 week, *t* = 4 weeks, *t* = 12 weeks, *t* = 6 months and *t* = 1 year (Figs. 3 and 4).

**Table 1 Tab1:** Outcome parameters and other parameters

Outcome parameters	
Behaviour change (stage of change)	Questionnaire containing 1 question per advice received to determine the current stage of change (transtheoretical model (Fig. 4) [43–45]).
Behaviour change (verification)	Physical activity: the validated Dutch version of the International Physical Activity Questionnaire (IPAQ) [46]. Smoking: questions on current smoking behaviour and quantity of smoking. Dietary and alcohol intake: questions on regular intake of all food groups and alcoholic consumptions, for which advice is received by the participant. Body weight and waist circumference: measured at home by the participant, following detailed instructions and using the same weighing scale each time.
Motivational regulation	Validated Treatment Self-Regulation Questionnaire (TSRQ) [47], translated into Dutch. This questionnaire has been modified to ask motivational regulation with regard to the ‘advice given’ and ‘healthy lifestyle’.
Attitude	Questionnaire consisting of 7 Likert scale items on outcome expectations, 16 Likert scale items on the reasons for (not) undergoing testing by Health Potential®, 50 Likert scale items on the attitude towards five primary lifestyle behaviours, 1 Likert scale item on the importance of preventing disease, and 6 items on the evaluation of the Health Potential® report.
Behaviour-specific self-efficacy	Questionnaire which was developed using the ‘Guide for constructing self-efficacy scales’ by Bandura [48]. It includes one self-efficacy question for each advice given in which the participant indicates on a scale of 0–100% how sure they are of their ability to follow the advice.
Risk perception	Likert scale questions on the perceived probability of getting and severity [37] of each of the diseases included in the standard Health Potential® service.
Perceived stress	Dutch translation of the validated 14-item Perceived Stress Scale (PSS) [49].
Discussion of test results with health professionals and/or family and friends	Multiple-answer question in which the participant can indicate with whom the results were discussed.
Test-related distress (arms 1 and 2 only)	Dutch translation [50, 51] of the validated Impact of Event Scale (IES), which has been used previously to study test-related distress after genetic testing for common disease risk [39].
Other study parameters	
Self-reported health status	Dutch translation of the validated RAND 36-Item Short Form Health Survey, V2 (SF-36 V2) [52, 53].
Health locus of control	Dutch translation of the validated Multidimensional Health Locus of Control (MHLC) Scale [54, 55].
Comprehension of risk estimates (arms 1 and 2 only)	Questions based on the questions used by Kaufman et al. [56].
Genetic knowledge (arms 1 and 2 only)	Dutch translation of the questions as used by Carere et al. [57].
Cue to action	Two Likert scale questions on whether the participant felt the Health Potential® report and the general health check were a cue to action.
Personal and family history of tested diseases	Questionnaire asking about personal and family history.
General self-efficacy	Validated Dutch General Self-Efficacy Scale (DGSES) [58].
Social modelling, social support	One Likert scale question per advice received.
Social support	One Likert scale question per lifestyle domain (diet, alcohol, physical activity, smoking, body weight).
Pro-active coping skills	Validated Utrechtse Pro-actieve Coping Competenties (UPCC) questionnaire [59].
Vitality	Validated Vita-16 [60].
Previous participation in genetic testing	Two yes/no questions.
Temporal discounting	Validated 10-item Delaying Gratification Inventory short form, translated into Dutch (DGI-10) [61].
Personality	Validated Dutch IPIP-50 [62].

